## Abstract

Chronic kidney disease (CKD) is associated with physical weakness and increased oxidative stress and inflammation levels. Rehabilitation programs are associated with an improvement in the functional capacity, inflammatory and oxidative stress profile. Exercise associated with blood flow restriction (BFR) has been demonstrating positive effects in training programs, but there is lack information about exercise with BFR in CKD. Therefore, the aim of the present study is to describe a protocol using continuous moderate exercise with blood flow restriction (BFR) applied during hemodialysis (HD) to measures health indicators and immune system and oxidative stress parameters in CKD patients. Methods: A RTC will be conducted with 42 patients in HD. Baseline measures will be compared with final measures (anthropometric, cardiorespiratory, biochemical, muscle fitness, nutritional and behavioral questions). Participants will be randomly allocated to: 1) Continuous moderate exercise group with BFR; 2) Continuous moderate exercise group without BFR; 3) Control group without exercise. The intervention will be 12 weeks long during HD session. Patients will perform 20 min of continuous moderate exercise on a stationary bicycle three times a week. The present study is expected to generate significant information about the role of exercise with BFR in patients with CKD during HD.

**Specifications Table**

**Table tbl0010:** 

**Subject Area**	• *Medicine and Dentistry*
**Reagents/tools:**	- *Ergometer cycle Oneal b2901d2* - *Cuff BFR Sistem (Hokanson)*
***Experimental design:**	Experimental randomized controlled trial (RCT), open-label, phase III-type study with 42 patients in HD. Baseline measures will be compared with final measures (anthropometric, cardiorespiratory, biochemical, muscle fitness, nutritional and behavioral questions). Participants will be randomly allocated to: 1) Continuous moderate exercise group with BFR; 2) Continuous moderate exercise group without BFR; 3) Control group without exercise. The intervention will be 12 weeks long during HD session. Patients will perform 20 minutes of continuous moderate exercise on a stationary bicycle three times a week during HD session The exercise will be performed in the first two hours of HD to avoid hypotension effects that occur usually in the second half of the 4-hour session.
**Trial registration:**	The study protocol was registered in the Brazilian Registry of Clinical Trials, under protocol RBR-8T2P2M.
**Ethics:**	The study protocol was submitted to the Research Ethics Committee of the Catholic University of Pelotas and approved under No. 2,036,385.
***Value of the Protocol:**	- This protocol is important to verify the effects of moderate intensity aerobic exercise associated with BFR. - There is a lack of knowledge about the effects of BFR in chronic diseases, and this work will help elucidate important points. - This rehabilitation protocol have a especific training program and will yield important results regarding the effects on the inflammatory profile, markers of oxidative stress and funcional capacity in chronic kidney patients.

## Description of protocol

Chronic kidney disease (CKD) is associated with physical weakness and increased oxidative stress and inflammation levels [1,2]. Rehabilitation programs are associated with an improvement in the functional capacity, inflammatory and oxidative stress profile.2] Exercise associated with blood flow restriction (BFR) has been demonstrating positive effects in training programs, but there is lack information about exercise with BFR in CKD [[3], [4], [5]]. Therefore, the aim of the present study is to describe of a protocol using continuous moderate exercise with blood flow restriction (BFR) applied during hemodialysis (HD) to measures health indicators and immune system and oxidative stress parameters in CKD patients.

### Design

An experimental randomized controlled trial (RCT), open-label, phase III-type study will be conducted, the SPIRIT (Standard Protocols Items: Recommendations for Interventional Trials) recommendations were followed, to evaluate the effectiveness of the BFR intervention. In addition, the data collection and the statistical analysis will be carried out by people unaware of the objectives of the study.

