### Randomization

The randomization process will be performed using the generation of random numbers in the Stata software, version 13, and the researcher who will carry out the process will be blinded regarding to the study objectives. The randomization will be done in blocks, each block referring to the HD shift. In each block, the first patient drawn will go to the BFRG, the second to the EG, the third to the CG, and so on. In total, 14 patients will be drawn in each block to ensure balance between groups.

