**Fig. 2 fig0010:**
[figure not shown]
Schedule of blood collections.

Serum levels of IL-6, IL-10, and CRP will be measured using immunoassay kit (DuoSet ELISA Development, R&D Systems, Inc., USA). These methods will follow the manufacturer's recommendations. The amount of IL-6, IL-10, and CRP will be determined by measuring the absorbance at 450 nm. All samples and standards will be measured in duplicate, and the coefficient of variation will be less than 5%. The IL-6, IL-10, and CRP levels will be expressed in pg/mL.

Oxidative stress markers (catalase, peroxide dismutase, and glutathione peroxidase enzymes) will be measured using a commercially available kit (RANSEL®; Randox Lab, Antrim, United Kingdom), using the method described by Misra and Fridovich [12].

The 6-minute walk test will be conducted on a 30-meter flat track, demarcated every three meters. Before starting the test, patients will remain seated for 10 min to stabilize vital signs. The patient will be advised to walk for 6 min, from one end of the lane to the other, at the highest possible speed. This test will be performed before the HD session, since patients cannot walk well after the HD session due to the loss of fluid with hypotensive effects [13].

The static strength testing of lower limbs will be performed with a Crown® brand dynamometer. Initially, patients will be instructed to stand on the base of the device, flexed knees forming an angle of approximately 120°, upright spine, arms along the body and extended elbows. After resetting the instrument, the subjects should perform the maximum knee extension force possible, avoiding any movement with the spine or arms and moving the body backwards. Two measurements will be performed with a 1 min interval between them. The mean of these two measures will be used as a result [14].

After baseline collection, participants will be allocated randomly: 1) BFRG; 2) EG; 3) CG. The intervention will last twelve weeks divided into three weekly sessions, always having at least a day interval between sessions. All physical exercise sessions will be monitored by physical therapists and physical education teachers to guarantee the perfect execution of the exercises and the correct use of the BFR accessory and heart monitor.

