### Data processing and analysis

The data will be doubled typed in EPIDATA 3.1 software, which will perform analysis to verify inconsistencies and correction of possible errors. The 5% significance level will be used and the statistical analysis will be conducted in Stata 14.0 software. The two mixed factors analysis of variance (ANOVA) will be used in the comparison of the training protocols, using Bonferroni as a post-hoc test for parametric variables. Kruskal-Wallis test and Dunn's post-hoc test will be used to non-parametric variables. The responsible researcher for the statistical analysis will be blinded regarding to the study objectives.

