### Quality control

To assure the quality control of the interviews, the main researcher will re-apply some key questions (previously defined) to 10% of the interviewees. The answers will be used to detect possible problems in the interviewer’s performance. If there is a problem, all interviews will be repeated. In addition, to ensure quality control, blood samples will be analyzed in triplicate, data will be typed in duplicate in EpiData3.1 software, and follow-up meetings will be held weekly with the staff members who will check physical training.

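### Data collectors and the analyst are blinded to the study objectives, not to treatment allocation, so as written they are free to know each patient's arm

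*Protocol article*

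**What the plan says.** The Design section declares the trial open: "An experimental randomized controlled trial (RCT), open-label, phase III-type study will be conducted". The same section adds a safeguard, that "the data collection and the statistical analysis will be carried out by people unaware of the objectives of the study".

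The safeguard appears twice more with the same object. Under Randomization, "the researcher who will carry out the process will be blinded regarding to the study objectives". Under Data processing and analysis, "The responsible researcher for the statistical analysis will be blinded regarding to the study objectives".

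On timing, the Procedures text after Fig. 2 states: "After baseline collection, participants will be allocated randomly". Baseline measures are thus taken before any arm exists, and the final measures after arms are assigned.

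Several of those final measures depend on effort or on the person measuring:

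- **6-minute walk:** "The patient will be advised to walk for 6 min, from one end of the lane to the other, at the highest possible speed".
- **Dynamometry:** "the subjects should perform the maximum knee extension force possible".
- **Quadriceps thickness:** a distance that the operator measures on a frozen ultrasound image (Procedures).
- **Quality of life:** a KDQOL-SF score collected within the study questionnaire (Questionnaire section).

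**The concern.** In an open-label trial, assessment is biased mainly through knowledge of who received what. An assessor who knows the arm can encourage one patient more than another on the walk or the dynamometer, place the measuring points differently on an image, or probe an interview answer differently. Staff who do not know the objectives can still do all of this. They need only know that one patient trained with cuffs, another without, and a third not at all, and hold an ordinary expectation that training helps.

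Patients and exercise supervisors cannot be masked here. The protection still available lies with the assessors, the image readers and the analyst, and that is where the article names the wrong target. Muscle thickness and quality of life are also two of the four outcomes on which the sample size is based (Sample size calculation).

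**Working it through.** The plan gives no figure to reproduce. The check has two parts: a reading of every blinding statement, and an illustration of scale.

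**1. What is masked, and for whom**

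| Role | Section | Masked to | Masked to allocation? |
|---|---|---|---|
| Data collectors | Design | Study objectives | Not stated |
| Analyst | Design; Data processing and analysis | Study objectives | Not stated |
| Randomising researcher | Randomization | Study objectives | Not applicable (this person generates the allocation) |

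No other section masks anyone. The article describes blinding three times and names the same object each time.

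**2. Which measures are exposed**

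The Study variables section lists eleven dependent variables. Six are laboratory assays (IL-6, IL-10, CRP and three enzymes) and depend little on the observer. The point rests on four others: ultrasound thickness, walk distance, strength and quality of life. Their baseline values precede allocation, so the exposure concerns the final values.

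**3. Is unawareness of the objectives itself secure?**

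Recruitment has the goals explained to every patient before permission is sought, so an interviewer may hear them from a patient. Under Quality control, "the main researcher will re-apply some key questions" to 10% of interviewees, and the main researcher can be presumed to know the objectives. Both sit uneasily with the Design statement.

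**4. Scale, as an illustration only**

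Inputs:

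- 42 patients and three arms (Abstract), so 42/3 = 14 per arm if the split is equal.
- Bonferroni post-hoc tests at 5% (Data processing and analysis).
- Assumed: three pairwise comparisons, and an assessor lean of 0.2 to 0.3 SD in favour of one arm. No document figure supports the lean.

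Formulas and results (normal approximation, difference of two arm means in SD units, no true effect):

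- Standard error = sqrt(1/14 + 1/14) = sqrt(2/14) = 0.378 SD.
- Per-comparison level = 0.05/3 = 0.0167, so the critical value is 2.394.
- False-positive rate = P(Z > 2.394 − s) + P(Z < −2.394 − s), where s = lean / 0.378.
- Lean 0.2 SD: s = 0.529; 0.0311 + 0.0017 = 0.033.
- Lean 0.3 SD: s = 0.794; 0.0548 + 0.0007 = 0.055 (0.0555 before rounding of the terms).

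So 1.7% becomes about 3.3% to 5.5%, or roughly 2 to 3.3 times the intended rate.

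The equal split matters little. Randomization draws 14 patients per dialysis shift and deals them in turn to three arms, which is 5, 5 and 4 per shift. If there are three shifts, the arms are 15, 15 and 12. For 15 against 12 the standard error is sqrt(1/15 + 1/12) = 0.387 SD, and the rates are 3.2% and 5.3%.

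**The case against.** The strongest reply is that this is a condensed article: it openly calls the trial open-label and nowhere says that assessors or the analyst are told the arm. A fuller document could contain allocation masking. The first part stands, and the point is worded accordingly: staff are free to know, not shown to know. The second part does not dispose of it. The article does not merely omit a detail; it specifies blinding three times and names an object that gives little protection. If objectives is a slip for allocation, it still needs correcting.

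Several stronger readings are tempting, and the document does not support them:

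- **That the Quality control section contradicts the Design section.** The re-interview is an audit of interviewer performance. The article does not say that its answers become trial data or that the key questions cover quality of life. It is a tension, no more.
- **That Table 1 proves the analyst sees the arms.** The table explains the codes 0, 1 and 2 to the reader. It does not say whether the analyst's file carries those meanings.
- **That assessors watch patients cycling with cuffs.** Therapists and physical education teachers monitor the sessions. Cycling takes place in the first two hours of dialysis, the walk test before dialysis, and the ultrasound 20 to 30 minutes after it. An assessor need not see training, although nothing prevents it.
- **That laboratory results or the choice of tests are compromised.** The assays depend little on the observer, coded tubes are a detail an article may leave out, and test selection may be settled in an analysis plan that is not shown.
- **That the false-positive rate rises from 5% to about 8-12%.** This follows from the same assumed lean only at an unadjusted 5% level, whereas the plan specifies Bonferroni for its parametric post-hoc tests.

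It is also fair to say that patients may disclose their arm in person. The most secure gain is therefore in the ultrasound reading and the analyst's file.

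**Conclusion.** The point holds in limited form. As written, the masking rule aims at the wrong target: data collectors and the analyst are kept from the objectives and not from the allocation. It applies to the final ultrasound thickness, 6-minute walk, strength and interview measures and to the analysis, and does not extend to the laboratory outcomes. It shows a correctable risk of bias, not that bias occurred or that the trial is invalid.

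The finding itself needs no number. The rise from 1.7% to about 3.3-5.5% per comparison rests wholly on the assumed lean of 0.2 to 0.3 SD, about 14 patients per arm and three Bonferroni-corrected comparisons. It also compares final means between two arms, which simplifies the planned mixed two-factor ANOVA. It should be read as an indication of sensitivity. The correction should be made because it is cheap, and because the Discussion expects strong evidence for implementing the programme, which unmasked observer-dependent outcomes would weaken.

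**What to change.** In Design and in Data processing and analysis, replace blinding to objectives with blinding to treatment allocation, and state how it is kept:

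- The planned data collectors perform the final ultrasound reading, walk, strength test and interviews without access to the allocation list, and do not supervise training.
- Ultrasound images carry study codes only.
- The analyst receives the arms as neutral codes A, B and C until the analysis is final.
- Where any of this was not or cannot be done, unmasked assessment of the outcomes concerned is reported as a limitation.

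The cost is revised wording, coded labels and control of access to the list. Treatment, visits and sample size do not change. If assessors and training supervisors are currently the same people, which the article does not settle, the duties would have to be divided. The remaining weakness is that patients may reveal their arm, so masking of the walk, strength and interview measures will be imperfect.

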### Subjects

HD patients from the Nephrology unit of the Hospital São Francisco de Paula in Pelotas, Southern Brazil, users of the Brazilian Health System (SUS), aged 18 years and older from both sexes.

### Exclusion criteria

For the exclusion criteria, we list possible associated pathologies that limit or are contraindicated for exercise prescription.a)Diagnosis of coronary artery disease, presence of active infection or cancer;b)Presence of musculoskeletal limitations preventing exercise performance;c)Cognitive alterations making it impossible to understand the instructions of the exercises;d)Systolic blood pressure ≥ to 180 mmHg or diastolic blood pressure ≥105 mmHg at rest; resting heart rate ≥ to 120 bpm.

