### Recruitment

Subjects will be recruited at the nephrology department, all chronic patients of the unit who is on hemodialysis treatment will be investigated in your medical records and basic information will be analyzed allowing the application of some exclusion criteria. Afterward, they will be individually interviewed and only who fill all criteria to be included, invited to participate in the study. Then, the goals of the study will be explained and the permission to perform the intervention will be solicited.

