**Fig. 1 fig0005:**

Intervention schedule.

The baseline measurements will be distributed at week 1 as follows. At the 1st HD session of the week the resting HR, resting blood pressure, ankle-arm index (AAI) measurements and questionnaire application will be performed. At the 2nd HD session of the week the percentage of fat, body mass and height measures, and blood collection will be obtained, after the HD session. At the 3rd HD session of the week the functional capacity (using the 6-minute walk test) and muscle strength (using dynamometry) will be measured. The final evaluations (post-intervention) will follow the same weekly distribution of the baseline measures.

Blood pressure will be measured with an accurate analog sphygmomanometer (accuracy of 1.0 mm/Hg) and stethoscope (BD, Brazil). Body mass and height will be measured using digital electronic anthropometric scale with a resolution of 0.1 kg and 0.1 cm, respectively (Filizola, Brazil). Body mass index (BMI) will be calculated based on body mass and height. The HR will be measured using a digital HR monitor (Polar, Finland).

To calculate ankle-arm index (AAI) the patient should rest supine for at least 10 min before testing, the systolic blood pressure measurement will be performed in the upper limb using an analog sphygmomanometer. The measure will be performed on the arm that is not with the dialysis fistula. The systolic blood pressure at the ankles will be measured using the vascular Doppler with transducer of 5–8 MHz with application of gel on the analyzed region and the same model of sphygmomanometer as previously reported [9]. The cuff will be placed about three inches above the malleolus. The following formula will be applied to calculate AAI: AAI = higher ankle pressure x higher arm pressure^−1^ [9].

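### The printed exclusion criteria address exercise but not the thigh cuff, so a patient with known peripheral arterial disease can be allocated to the blood flow restriction arm

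*Protocol article*

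**What the plan says.** **Eligibility.** The Exclusion criteria section gives a lettered list, a) to d), and states its purpose: "we list possible associated pathologies that limit or are contraindicated for exercise prescription". The Subjects section adds only that participants are haemodialysis adults of either sex at one unit. Under Recruitment, medical records are searched first, and "basic information will be analyzed allowing the application of some exclusion criteria". An individual interview follows, and then the invitation.

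**The cuff.** Under Intervention description, BFRG wears a 6 cm band high on the thighs. The pressure is 100, 130, 150 or 180 mmHg, read from a table of thigh circumference, and it is kept up for the whole 20-minute bout.

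**The ankle-arm index.** Under Procedures, at the first dialysis session of the baseline week, "resting HR, resting blood pressure, ankle-arm index (AAI) measurements and questionnaire application will be performed". On the method, "The systolic blood pressure at the ankles will be measured using the vascular Doppler". Allocation comes later: "After baseline collection, participants will be allocated randomly". The Study variables section lists the index as a dependent variable. No cut-off is printed, and no link to eligibility or cuff pressure.

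**Safeguards during sessions.** "All physical exercise sessions will be monitored by physical therapists and physical education teachers", among other things so that the cuff is used correctly. Exercise also stops if the patient is uncomfortable or asks to stop.

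**The concern.** The feature that separates BFRG from the other exercise arm is a pressurised band on the thigh. Eligibility should therefore screen for conditions that make the band unsuitable as well as those that make cycling unsuitable. Arterial disease of the legs is the obvious candidate, and it is absent from the list.

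What is at stake is participant safety. Someone whose disease is already in the records could be enrolled, drawn to BFRG and cuffed, with protection left to staff vigilance and the patient's own report of discomfort.

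There is a secondary point about comparability. If staff dealt with such patients informally after allocation, only BFRG would be affected, and the randomised comparison would suffer. A rule applied before the draw to everyone avoids that.

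**Working it through.** The plan prints no figure on this point, so there is nothing to reproduce. The check sets the sections side by side.

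1. **Does any exclusion cover leg arterial disease?** Item a) names coronary artery disease, active infection and cancer. Item b) is musculoskeletal. Item c) is cognitive. Item d) sets limits for resting blood pressure and heart rate. None covers the leg arteries, and the Subjects section adds no vascular condition.

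2. **Does the cuff rule adapt to the patient's circulation?** No. Pressure depends on thigh circumference only; neither the ankle-arm index nor a limb pressure enters.

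3. **What is known, and when?** From Recruitment, Procedures and Randomization the order is: record review and interview; invitation and consent; baseline week, with the index at the first session; random allocation; training. A recorded diagnosis is thus available before invitation, and the index before the draw.

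4. **Follow one patient through.** Suppose the records show peripheral arterial disease and none of a) to d) applies. The patient is eligible, is invited, consents and has the index measured. The patient then enters the draw, where "In each block, the first patient drawn will go to the BFRG, the second to the EG, the third to the CG". The chance of BFRG is about one in three (42/3 = 14 per arm if the arms are equal). In BFRG the patient is cuffed at the pressure for that thigh circumference. No printed step stops this before allocation.

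5. **What do the safeguards do?** Both belong to the training sessions, which follow allocation. They may limit harm, but they do not decide who enters BFRG.

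6. **Size.** The number affected would be the number of enrolled patients with the disease, times about one third. The article gives no prevalence, so the first factor is unknown and no count is offered.

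**The case against.** **The premise comes from outside the document.** Nothing in the article says that leg arterial disease rules out partial restriction, and no statement is contradicted. That is true, and the point is put as a clinical premise. It is a modest one, needing no cited figure: a pressurised thigh band carries risk where arterial supply is already poor.

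**The article is condensed, and the list is not declared complete.** A fuller protocol could hold more device screening. This stands as a limit on confidence. Still, the article prints lettered criteria with their rationale, and that rationale concerns exercise.

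**Exercise could be read to include cuffed exercise.** A clinician might take the introductory sentence that way and exclude such patients. No listed item requires it, so practice would depend on who screens.

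Four stronger readings are tempting and are not supported:

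- *A cut-off on the ankle-arm index is a necessary exclusion that the plan omitted.* The article gives no limit, and excluding on the index would truncate one of the trial's own outcomes. Review of the index is therefore offered only as an option.
- *The 50% arterial restriction target will be missed in patients with a low index.* An ankle-to-arm ratio does not establish arterial pressure at the thigh. No claim is made about that target.
- *Total cuff exposure measures the problem.* Twelve weeks of three 20-minute sessions give at most 12 × 3 × 20 = 720 minutes per BFRG patient. That describes everyone in the arm, not those with arterial disease.
- *The safeguards act only once the cuff is inflated.* The article has the band put on before it is inflated and has staff watch over its correct use, so supervision may begin before inflation. It is still not an entry check.

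**Conclusion.** The point holds as a gap in eligibility and participant safety. The printed criteria are framed around exercise and omit leg arterial disease, while one arm receives a thigh cuff at 100 to 180 mmHg set by circumference alone. A patient with known peripheral arterial disease can therefore reach BFRG under the plan as written.

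The conclusion rests on two assumptions: that the printed list is the operative one, and that poor arterial supply makes a thigh cuff inadvisable. The number of patients affected is unknown. The point implies no error in the planned analysis or in any stated figure.

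**What to change.** **Main change.** Add known peripheral arterial disease to the exclusion criteria. Apply it to all three arms before randomisation, from the medical records already searched under Recruitment. The cost is a line of wording, a slightly smaller eligible pool at a single unit, and conclusions limited to patients suitable for blood flow restriction.

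**Optional addition.** Before the draw, have a clinician review the baseline ankle-arm index of each leg against a limit the clinical team sets in advance, in the same way for every patient whatever the arm. Each leg needs its own value, because the printed formula takes the higher ankle pressure and can hide disease on one side. This option costs more. The index is measured after consent, so some consented patients would fail screening and need replacing before the draw, given that "14 patients will be drawn in each block to ensure balance between groups". The index would also span a narrower range as an outcome.
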